#### **11.7.3 Protecting against bias**

Minimization of selection and confounding bias will be achieved through central block randomisation taking baseline data on malaria risk into account. The matched design with villages as the unit of randomisation will minimize contamination between individual villages and avoid allocation errors.

#### **11.7.4 Data Analysis**

The % of children receiving IPTpd according to schedule will be compared by relative risks (95% CI), adjusted for prognostic factors at baseline using log binomial or Poisson regression with adjustment for cluster effects. Hazard ratios will be calculated for morbidity endpoints using Cox regression for repeated events with robust standard error estimation methods to account for correlation between episodes within children. Incidence rates per child-year and absolute rate reductions will also be calculated.

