| Outcomes                            |                         |                               |                       |                                                                                                                                                                           |          |          |                      |          |          |                         |           |           |                       |
| PMC uptake                                 |                         |                               |                       | X                                                                                                                                                                         | X        | X        | X                    | X        | X        | X                       | X         | X         |                       |
| Clinic visits, Adverse events              |                         |                               |                       | Passive surveillance in clinics in the catchment area, 26 weeks from 0-26 weeks (clinical malaria and other acute illnesses) (RDT/smear, Hb, and other tests as required) |          |          |                      |          |          |                         |           |           |                       |
| Hospitalisation                            |                         |                               |                       | Passive surveillance for hospital admission in the catchment area, 26 weeks from 0-26 weeks                                                                               |          |          |                      |          |          |                         |           |           |                       |
| Vital status                               |                         |                               | X                     | X                                                                                                                                                                         |          |          |                      | X        |          |                         |           | X         | X                     |

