##### 8.7.4.2 Randomisation procedure at discharge

The unit of randomization will be the villages, defined as the smallest administrative unit overseen by a Village headman. A group Village headman oversees several villages. Ninety (90) villages in the catchment areas of Zomba district located in the southern region of Malawi will be involved in the study. Zomba Central Hospital participated in previous related studies [1, 15-17] and is particularly suitable for the delivery trial because of the existing linkages with community based health care providers and rural clinics within their catchment areas. A 1:1 allocation ratio will be used. To minimize imbalances across groups with respect to baseline malaria prevalence and risk factors for malaria, location-specific baseline information on malaria indicators, such as the prevalence of positive RDTs or microscopy in the 12-month period prior to the trial (Under-five registry data) will be considered in selection of villages.

Randomisation will be done by opening a single concealed envelope, which will contain the cluster and study arm.

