## 8.8 PARTICIPANT WITHDRAWAL

Patients can discontinue from the study for any one of the following reasons.

1. Screening error resulting in incorrect enrolment (found that subject did not meet required inclusion / exclusion criteria)
2. Withdrawal of consent at any stage or subject not willing to continue in the study / voluntary discontinuation by the subject
3. Suspected or confirmed allergic reaction to the study drug (removal from therapy only)
4. Safety reasons as judged by the investigator, study safety monitor or DMEC (removal from therapy only)
5. Other

The parents or guardian of subjects who discontinue from the study treatment or from the study entirely will always be asked about the reason(s) for their discontinuation and the presence of adverse events. If a subject discontinues it should be established whether the subject:

1. Discontinues the study treatment, but continues their consent for the data capture up to that point, and to continue follow-up. These subjects will be considered 'off study drug/on study' and where feasible will follow the same schedule of events as those who continue the study intervention, except any adherence assessment. All of these children will be followed until study end at 6 months from enrolment.
2. Discontinues all future activities in the study, but continues their consent for the data captured up to that point to be used in the research
3. Discontinues all future activities in the study and withdraws consent for any data captured to be used for the research

Every effort will be made to follow-up patients who discontinue due to drug related adverse events in order to determine the final outcome. If a subject discontinues due to drug-related adverse events, all the assessments will be conducted that would have been carried out at the next scheduled visit at 6 month (unless consent is withdrawn). This will be recorded in the Case Record Forms (CRFs). The study drug will be returned by the subject. Subjects that have discontinued the study prematurely will not be replaced.

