### 8.10 EXPECTED DURATION OF TRIAL

The total duration of the trial for a participating mother/guardian-child pair is 3.5 months. Participant recruitment will occur for 30 months. There will be 4 months of follow-up of the last recruited subject and finally 6 months to complete data analysis and study reporting. The end of trial will be defined as the final assessment of the last participant within the trial, unless additional time is needed for follow-up of a trial-associated adverse event. This new protocol is a continuation of COMREC study P.02/15/1679.

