#### **11.7 STATISTICS AND DATA ANALYSES**

##### **11.7.1 Sample Size and randomization**

Although a 2x2 factorial design will be used, only the main effects of "place of delivery" and "use of mobile phone reminders" are of primary interest. Each village cluster contributes 2 to 4 children/y with severe anaemia and there are 102 clusters in the catchment area. Assuming an intra-cluster correlation coefficient (ICC) of 0.1 and allowing for 20% loss-to-follow-up or efficiency loss due to varying cluster sizes, a sample size of 19 clusters of 5 children per arm (95 per arm, N=380 overall) has 80% power to detect a 25% absolute increase in coverage from an estimated 50% in the standard VHV or OPD groups to 75% in the arms supported by mobile phone reminders ( $\alpha=0.05$ ). The ICC of 0.1 is slightly more conservative than the ICC in a previous trial of delivery approaches for IPTc in the Gambia (0.08)[14].

The trial will use villages as the unit of randomisation; i.e. it is a cluster-randomised trial. This trial uses a factorial design and will evaluate two interventions, and will have 4 arms (factorial design). These kind of trials need to take the clustering in variation at village level into account, also called the design effect.

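### The morbidity Cox models set the robust variance at the child, not the randomised village, and the sections give different ends of follow-up

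*Protocol*

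**What the plan says.** **Level of correlation.** Section 8.7.4.2 of the protocol fixes the design: "The unit of randomization will be the villages". Section 11.7.1 states the consequence: "These kind of trials need to take the clustering in variation at village level into account, also called the design effect". Section 11.7.4 follows this for uptake, which is to be analysed by "log binomial or Poisson regression with adjustment for cluster effects". Its next sentence covers the morbidity endpoints: Cox regression for repeated events, with "robust standard error estimation methods to account for correlation between episodes within children". Village is not mentioned there. Section 11.7.4 also promises incidence rates per child-year and absolute rate reductions.

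**End of follow-up.** Section 8.10 says: "The total duration of the trial for a participating mother/guardian-child pair is 3.5 months". Table 2 in Section 4.2 has: "Passive surveillance for hospital admission in the catchment area, 26 weeks from 0-26 weeks", and the same span for clinic visits. Section 8.8, on children who stop study drug but stay in the study, says: "All of these children will be followed until study end at 6 months from enrolment". Other sections give 14 or 15 weeks; they are set out in the working below.

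**The concern.** A robust variance corrects for correlation inside the unit it is clustered on. Clustering on the child handles repeat episodes but treats two children of one village as independent, although they were allocated together. The protocol itself expects malaria risk to vary by place: Section 8.7.4.2 uses local malaria indicators in choosing villages, and Section 11.7.3 takes baseline malaria risk into account in the randomisation. The outcomes concerned include readmission for severe anaemia or severe malaria and visits for confirmed malaria, so some village correlation is plausible. These comparisons serve the safety objective (Section 7.2, objective 3).

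The protocol does more than leave a detail to the analysis plan. It names a correlation level for morbidity and names the wrong one, so an analysis plan that followed the sentence literally would carry the error.

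The end of follow-up matters to the same analyses, because it sets the censoring time and the child-years denominator of every rate.

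**Working it through.** **Inputs**
- Section 8.3: ICC 0.1 (for uptake), mean cluster size m = 3, CV² = 0.036, 10% loss, 50% versus 75% uptake, 80% power, 75 children per arm.
- Sections 4.1 and 8.2: 375 children and 90 villages, so 375/90 = 4.17 per village.
- Assumed: a morbidity ICC of 0.02 to 0.10, since none is given; a two-sided 5% level.

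**The plan's own figure.** Unpooled two-proportion formula: n = (1.960 + 0.842)² × (0.50×0.50 + 0.75×0.25) / 0.25² = 7.85 × 0.4375 / 0.0625 ≈ 55. Design effect DE = 1 + ((1 + CV²)m − 1) × ICC = 1 + (1.036×3 − 1) × 0.1 = 1.211. Then 55 × 1.211 / 0.9 = 74.0, which is 25 villages of 3, or 75 per arm. Section 8.3 is reproduced, so this is the right design effect to carry over.

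**Effect of omitting village.** The standard error is too small by 1 − 1/√DE, and the actual error of a nominal 5% test is 2(1 − Φ(1.96/√DE)).

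| m | ICC | DE | √DE | SE too small by | Actual error |
|---|---|---|---|---|---|
| 3 | 0.02 | 1.042 | 1.021 | 2% | 5.5% |
| 3 | 0.10 | 1.211 | 1.101 | 9% | 7.5% |
| 4.17 | 0.02 | 1.066 | 1.033 | 3% | 5.8% |
| 4.17 | 0.10 | 1.332 | 1.154 | 13% | 8.9% |

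The rows at 4.17 keep the CV that Section 8.3 derives for a mean of 3, so they are an approximation.

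**Simulation check.** Recurrent events were simulated with 25 villages per arm, 2 to 4 children per village, 0.27 years of follow-up and a child frailty variance of 0.5. The village frailty variances and event rates are assumptions. Coverage of nominal 95% intervals:

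| Village frailty variance | Events per child-year | Clustered on child | Clustered on village |
|---|---|---|---|
| 0 | 1 | 94.8% | 94.5% |
| 0 | 3 | 94.7% | 94.5% |
| 0.25 | 1 | 93.5% | 94.4% |
| 0.25 | 3 | 91.4% | 94.0% |
| 0.5 | 1 | 91.6% | 93.7% |
| 0.5 | 3 | 88.5% | 93.4% |

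Without village variance, clustering on the child is adequate. With it, coverage falls, and clustering on village recovers most of the loss. The remaining shortfall is why a small-sample correction is needed.

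**End of follow-up, side by side**
- 14 weeks or 3.5 months: Table 1 footnote and Table 2 study-end visit (Section 4.2); Section 8.10; the sick-visit period in Section 8.12.1.
- 15 weeks: follow-up procedures in Section 4.2; Sections 8.7.6.2 and 8.12.5; the end visit in Section 8.12.1.
- 0–26 weeks: surveillance rows of Table 2.
- 6 months: exclusion criteria in Section 8.7.4.4; Section 8.8.

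Planned child-time per child therefore differs by up to 26/14 = 1.86. The 14- and 15-week figures can overlap, because Table 2 allows the end visit on day 98 ± 7, and day 105 is week 15. The larger gap is to 26 weeks or 6 months.

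**The case against.** **On the variance.** Section 11.7.1 already states in general terms that village clustering must be taken into account, the primary uptake analysis does so, and an analysis plan could extend it to morbidity. The 0.1 in Section 8.3 is an ICC for uptake; if morbidity has no village correlation, nothing is lost. The matched design (Sections 11.7.2 and 11.7.3) could offset part of the effect if the matching were modelled. All of this limits the size and reach of the point. It does not remove it: Section 11.7.4 names the child for these models, and it does not model the matching. A reader might infer that the morbidity intervals are certainly too narrow, or that the primary result is in doubt. The protocol supports neither.

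**On follow-up.** A reader might infer from Sections 8.10 and 8.8 together that children who stop study drug are planned to be followed nearly twice as long as the rest, so that follow-up depends on adherence. The text does not support this. Section 8.8 puts children off drug on the same schedule as the others where feasible and treats 6 months as the end of the study. Section 8.7.4.4 uses 6 months as the study length for everyone, and Table 2 applies 26 weeks without restriction. Section 8.8 also concerns formal discontinuation, not missed doses. These are conflicting study lengths, not planned differential follow-up.

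Nor does it follow that events after week 15 would be missed. Section 8.8 refers to a scheduled visit at 6 months, Table 2 provides surveillance across the catchment area, and Sections 8.7.5.2 and 8.12.6.2 provide for reporting of deaths and verbal autopsy. Under-ascertainment is possible but not shown.

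**Conclusion.** The point holds in two separate parts.

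First, Section 11.7.4 sets the wrong correlation level for the morbidity hazard ratios, contrary to the protocol's own rule. The effect is conditional and modest. If the village ICC for morbidity lies between 0.02 and 0.10, an assumption the protocol can neither confirm nor exclude, standard errors are 2–9% too small at 3 children per village and 3–13% at 4.2. The corresponding error rates are 5.5–7.5% and 5.8–8.9% for a nominal 5%. With zero village correlation there is no error. Only the secondary and safety outcomes are touched.

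Second, the protocol gives incompatible ends of follow-up, so the censoring time and the child-years are undefined by a factor of up to 1.86. Which length was intended cannot be read from the text, and no bias between arms or by adherence is demonstrated.

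**What to change.** In Section 11.7.4, cluster the robust variance on village for all Cox and incidence-rate analyses. Children are nested in villages, so this also covers repeat episodes within a child, and no second adjustment is needed. Add a small-sample correction for the number of villages: 90/5 = 18 per arm by Section 8.2, or 25 per arm by Section 8.3. This is about one sentence, and the cost is slightly wider intervals, about 1.02 to 1.15 times over the range assumed above.

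Separately, reconcile Section 4.2 (follow-up text, Table 1 footnote and Table 2) with Sections 8.7.4.4, 8.7.6.2, 8.8, 8.10, 8.12.1 and 8.12.5. State one common censoring time for clinical outcomes that applies to every child, on or off study drug. The investigators must say which length was meant; this review does not presume it. The correction itself is editorial.

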### **12 Result dissemination and publication policy**

This study is part of the activities of the PMC Consortium funded through the Norwegian GLOBVAC programme to conduct these ancillary studies in Malawi, Uganda and Kenya aimed at generating the evidence needed by the World Health Organisation to consider PMC as a strategy to reduce post-discharge morbidity and mortality in malaria endemic areas in Africa.

At the end of the trials, the results will firstly be disseminated to national policy makers, government departments, academics from local research institutions and universities, and professional bodies in Malawi at the College of Medicine Research Dissemination conference as well as specific stakeholder fora. Based on consensus emerging at these meetings, project partners in Malawi will support national policy makers to develop the necessary tools and guidelines to guide national and district level health providers to implement the PMC strategy within hospital services and the health system more broadly.

Research results will also be disseminated to the global malaria research community, technical agencies, and international government bodies via peer reviewed journals and at international scientific fora, including the annual American Society of Tropical Medicine and Hygiene (ASTMH) meeting in 2015 or 2016, the Multilateral Initiative on Malaria (MIM) in 2017, and via meetings at WHO in Geneva comprised of leading scientists in the field of malaria.

We will also inform other international organisations and funders of large scale malaria control initiatives including DFID, USAID and the US President's Malaria Initiative (PMI) which aim to improve malaria at regional and local levels and are instrumental in supporting countries to implement malaria control policies in Africa.

Lastly, the investigators will publish the results of this research scientific peer reviewed journals.

### **12.1 AUTHORSHIP AND PUBLICATIONS**

The study will have a publications committee that will be part of the PMC Consortium created by the partners funded through the Norwegian Globvac programme to conduct this and these ancillary studies in Malawi, Uganda and Kenya aimed at generating the evidence needed by the World Health Organisation to consider PMC/IPTpd as a strategy to reduce post-discharge morbidity and mortality in malaria endemic areas in Africa. The core membership of the Publication Committee will consist of the Consortium grant holders (KP and BR), the Chief Investigator of this trial (FtK), site-principal investigators (Kenya MD and SK, Uganda CJ and RI) from each participating country and the leads of the ancillary studies (BR and MC). For each manuscript a writing committee will be formed. Each participating country group is requested to suggest and justify names for authors in addition to the CI and PIs, to be reviewed by the publications committee. Potential site authors could include all professionals that have participated in the trial for a minimum of one year. It is anticipated that for the publication of the results of the main trial, the CI will have last authorship and that a PhD student or one of the site PIs will have lead authorship. It is also anticipated that the PI of an ancillary study should be considered for the first choice for lead or last author of material derived from this study. Authorship of any presentations or publications arising from this study will also be governed by the principles for authorship criteria of the International Committee of Medical Journal Editors has designed. Disputes regarding authorship will be settled by the CI, PIs and chair of the publications committee.

### **12.2 INSURANCE / INDEMNITY**

A trial insurance policy will be taken out by the sponsor in country.

### **12.3 FINANCIAL ASPECTS**

Funding to conduct the trial is provided by the Globvac programme, the Research Council of Norway, project identification 234487.

## **13 Capacity building**

### **13.1 TRAINING, FELLOWSHIPS AND CAPACITY BUILDING**

Research capacity will be enhanced by provision of training and mentorship for research staff. By running this trial, capacity in trial management will be enhanced in addition to which north partner staff will provide support to write new proposals for research funding for beyond the end of the trial. The research study will strengthen the clinical skills of health workers in managing patients.

CIH has for many years spearheaded Norway's efforts in global health research, and has conducted high-impact research in the area of child health. Over the last 5 years, CIH successfully trained 55 MSc students and 112 students completed their PhD training at the research school in international health ([www.uib.no/rs/ih](http://www.uib.no/rs/ih)), (50 the last 5 years). There will be 1 PhD candidate who will conduct his/her research as part of this project with a thematic area in epidemiology, and/or medical statistics. Partners from the different institutions forming this research network will jointly supervise them. They will be required to present their scientific work during PMC meetings where their general academic progress will be discussed. There is dedicated PhD space at the College of

Medicine with internet and library facilities. The field site will have dedicated area for PhD and other students with dedicated internet facilities. The PhD will have small funds to support educational materials and travel to conferences.

### **13.2 AFRICAN LEADERSHIP**

This program will offer the PI (PhD qualified 6 years ago) the opportunity to learn to lead a large multi-country multi-disciplinary project supported by Profs [name] and [name], and will offer the opportunity for [name], the study statistician to get exposure to multi-centre clinical trials. He will benefit from the involvement of [name] (LSHTM) and the trial statistician at CDC. A Norwegian Post-doc will benefit from a 1-year assignment at the Imperial College London and LSHTM.

## **14 Ethics & Regulatory Approvals**

### **14.1 DECLARATION OF HELSINKI**

The trial will be conducted in compliance with the principles of the Declaration of Helsinki (1996), the principles of GCP and in accordance with all applicable regulatory requirements in Malawi.

### **14.2 RESEARCH ETHICS COMMITTEE AND INSTITUTIONAL REVIEW BOARDS**

This protocol and related documents (informed consent and participant information sheets) will be submitted for review to the Institutional Review Boards (IRB) and Research Ethics Committees at the Malawi College of Medicine.

Any protocol amendments will be submitted to the primary ethics committees before implementation. The study will comply with local regulations pertaining to reporting of SAEs and in addition will report safety data to Sigma Tau, the manufacturer of DHP. A copy of the final study report will be provided to all RECs, DMEC, regulator, and Sigma Tau.

### **14.3 INFORMED CONSENT**

Informed consent will be obtained from each participant and documented appropriately before children are enrolled in the study (see appendix). The carers will be given the informed consent form to read, with the help of the trial staff, and the carers will be given a chance to ask questions. The carers will be given a copy of the consent form. Carers who are able to sign their name will be asked to sign the consent form. For a carer who cannot read (non-literate), the informed consent will be read to the carer by a member of the study team, and documented by thumbprint. Carers who consent using a thumbprint will have a witness who attests the consent was read to them in its entirety, and that their participation was voluntary. Details about the trial and its benefits and potential risk will be explained to the participants in the language in which they are most fluent.

